## Abstract

**Background:** Repetitive peripheral nerve sensory stimulation (RPSS) has emerged as a potential adjuvant strategy to motor training in stroke rehabilitation. The aim of this study is to test the hypothesis that 3 h sessions of active RPSS associated with functional electrical stimulation (FES) and task-specific training (TST) distributed three times a week, over 6 weeks, is more beneficial to improve upper limb motor function than sham RPSS in addition to FES and TST, in subjects with moderate to severe hand motor impairments in the chronic phase (>6 months) after stroke.

**Methods:** In this single-center, randomized, placebo controlled, parallel-group, double-blind study we compare the effects of 18 sessions of active and sham RPSS as add-on interventions to FES and task-specific training of the paretic upper limb, in 40 subjects in the chronic phase after ischemic or hemorrhagic stroke, with Fugl-Meyer upper limb scores ranging from 7 to 50 and able to voluntarily activate any active range of wrist extension. The primary outcome measure is the Wolf Motor Function Test (WMFT) after 6 weeks of treatment. The secondary outcomes are the WMFT at 3, 10, and 18 weeks after beginning of treatment, as well as the following outcomes measured at 3, 6, 10, and 18 weeks: Motor Activity Log; active range of motion of wrist extension and flexion; grasp and pinch strength in the paretic and non-paretic sides (the order of testing is randomized within and across subjects); Modified Ashworth Scale; Fugl-Meyer Assessment-Upper Limb in the paretic arm; Barthel Index; Stroke Impact Scale.

**Discussion:** This project represents a major step in developing a rehabilitation strategy with potential to have impact on the treatment of stroke patients with poor motor recovery in developing countries worldwide. The study preliminarily evaluates a straightforward, non-invasive, inexpensive intervention. If feasibility and preliminary efficacy are demonstrated, further investigations of the proposed intervention (underlying mechanisms/ effects in larger numbers of patients) should be performed.

**Trial Registration:** NCT02658578.

## Introduction

Upper limb paresis occurs in up to 80% of subjects with stroke. Six months after stroke, two-thirds of survivors are not able to perform activities of daily living using their paretic hand and often do not return to work (1, 2). The catastrophic burden of stroke and the paucity of evidence-based rehabilitation interventions to decrease upper limb disability prompted research about effects of somatosensory stimulation in the form of repetitive peripheral nerve sensory stimulation (RPSS) to enhance motor function.

In RPSS, trains of electric pulses are delivered to peripheral nerves by surface electrodes. Intensities of stimulation are adjusted in order to elicit paresthesias, but not pain or movements, in the territory of the stimulated nerve. The goal of this intervention is to provide controlled enhancement of sensory input from the stimulated body part. The paradigm of stimulation was based on reports of changes in the sensory and motor cortices of animals induced by specific patterns of sensory stimulation. Duration of pulses of 1 ms and the frequency of bursts (10 Hz, 500 ms on, 500 ms off) were chosen to optimally activate proprioceptive and large cutaneous sensory fibers (3).

In 2000, in the first publication about RPSS in humans, ulnar nerve stimulation led to increase excitability of the motor cortex to transcranial magnetic stimulation in healthy subjects (4). Other studies confirmed and extended these findings (5–7). The encouraging results in healthy subjects and the key role played by sensory input on motor recovery in subjects with stroke (8) fostered research about the effects of RPSS on motor control of patients with upper limb paresis. In 2002, preliminary results indicated that a single session of RPSS might enhance strength of the paretic hand in subjects with stroke (9). Since then, other studies reported benefits of single or repeated sessions of RPSS in stroke [for a systematic review, see Conforto et al., (10)]. The bulk of the work of RPSS in stroke had focused in patients with mild to moderate motor impairments until 2016, when improvements exceeding minimal clinically important differences in the Active Research Arm Test, were reported in patients with moderate to severe impairments when 2-h RPSS was followed by 4 h of intensive task-oriented motor training for ten consecutive weekdays (11).

Six hours of daily rehabilitation for 10 days over 2 weeks may not be a feasible strategy in developing countries where the greatest disability from stroke occurs (12). Here, we report the design of the study “Peripheral Nerve Stimulation and Motor Training to Enhance Hand Function After Stroke” (ClinicalTrials.gov identifier NCT02658578). The aim of this study is to test the hypothesis that 3-h sessions of active RPSS associated with functional electrical stimulation (FES) and task-specific training (TST) distributed three times a week, over 6 weeks, is more beneficial to improve upper limb motor function than sham RPSS in addition to FES and TST, in subjects with moderate to severe hand motor impairments in the chronic phase after stroke.

## Methods and Analysis

### Design

In this single-center, randomized, placebo controlled, parallel-group study we compare the effects of 18 sessions of active and sham RPSS as add-on interventions to FES and task-specific training of the paretic upper limb, in subjects in the chronic phase after stroke. Patients are naïve to the hypotheses of the study. Patients and researchers responsible for evaluation of outcomes are blinded to treatment allocation. Figure 1 shows the flow diagram of the trial.

**Figure 1 F1:**
[figure not shown]
Flow chart.

### Location and Setting

The study is being conducted at the Neurostimulation Laboratory at Hospital das Clínicas/São Paulo University in São Paulo, Brazil. Brazil is characterized by extreme social disparities and 4 in 5 inhabitants do not have private health insurance (13). Access to the public services is limited, in particular for specialized care such as neurological clinics and stroke rehabilitation. The majority of the population that receives care at Hospital das Clínicas/São Paulo University, the largest public, academic hospital in South America, is socially and economically disadvantaged. In the city of São Paulo, 1/3 of all subjects, and 1/2 of elderly subjects who attended university hospitals were found to be illiterate (14). In a study performed in our Emergency Department in São Paulo in 2003, 94.4% of the patients did not have private health insurance and 54.5% of the patients had >4years of education (15).

### Participants

#### Eligibility Criteria

Eligibility criteria are shown in Table 1. The ability to perform finger extension was not a prerequisite for inclusion.

**Table 1 T1:** Eligibility criteria.

**INCLUSION CRITERIA**
18 years or older
Ischemic or hemorrhagic stroke at least 6 months before, confirmed by computed tomography or magnetic resonance imaging
Moderate to severe motor upper limb impairment defined as a score between 7 and 50 in the Fugl-Meyer Assessment of sensorimotor recovery after stroke (0–66) (15)
Ability to provide written informed consent (patient or legal representative)
Ability to comply with the schedule of interventions and evaluations in the protocol
**EXCLUSION CRITERIA**
Lack of ability to voluntarily activate any active range of wrist extension
Anesthesia of the paretic hand
Lesions that affect the cerebellum or cerebellar/vestibular pathways in the brainstem
Severe spasticity at the paretic elbow, wrist, or fingers, defined as a score of >3 on the Modified Ashworth Spasticity Scale
Active joint deformity
Uncontrolled medical problems such as end-stage cancer or renal disease
Pregnancy
Seizures, if current use of drugs that may decrease seizure threshold such as tryciclic antidepressants
Pacemakers
Other neurological disorders such as Parkinson's disease
Psychiatric illness including severe depression
Aphasia or serious cognitive deficits that preclude comprehension of the experimental protocol or ability to provide consent
Treatment of upper limb spasticity with botulinum toxin within the past 3 months

We expect to include patients with low levels of education, reflecting the characteristics of our population, shared with those of other low- and middle- income countries.

We include patients with ischemic or hemorrhagic stroke because even though mortality in the acute phase is greater in hemorrhagic than in ischemic strokes, survivors of hemorrhagic strokes and ischemic strokes with comparable impairments have similar responses to rehabilitation interventions (16, 17).

We do not include patients with hand anesthesia because there is evidence that RPSS exerts its effects by enhancing excitability in the sensorimotor cortex (4, 5, 7, 18, 19) and therefore, residual sensory function and partial integrity of cortical motor neurons are likely to be necessary for the beneficial effects of RPSS.

Children will not be included in the study because the question addressed by the proposal involves adult stroke patients. Stroke is rare in children, and the epidemiological profile, treatment, and prognosis of stroke is different in children than adults. Activities of daily living are also different in different developmental stages. The interventions in the current proposal are based on activities commonly performed by adults in daily living. Therefore, inclusion of children is inappropriate in the current proposal. A separate, age-specific study in children is warranted and preferable.

We exclude pregnant women because safety of RPSS has not been determined in this group. The study does not include other vulnerable populations such as prisoners or institutionalized individuals.

We exclude patients with other neurological disorders and psychiatric illness to prevent bias in the investigation of the experimental hypotheses. For the same reason, patients and caregivers are blinded to the experimental hypotheses.

#### Recruitment

Subjects are recruited in the community through advertisements on websites or local radio stations, and also among patients from the Stroke group/Neurology Clinical Division, Hospital das Clinicas/São Paulo University.

#### Subjects' Characteristics

The following characteristics are evaluated at baseline: age, gender, ethnicity, years of education, medications, time from stroke, type of stroke (ischemic/hemorrhagic), lesion side/location, scores in the National Institutes of Health Stroke Scale (NIHSS), (20) Modified Rankin Scale, (20) Minimental State Examination, (21) handedness prior to the stroke according to the Oldfield Inventory, (22) spasticity in elbow, wrist and finger joints in the paretic upper limb according to the Modified Ashworth Scale (MAS), (23) scores in the Fugl-Meyer Assessment of Sensorimotor recovery (upper limb—FMA-UL), (24, 25) Barthel Index (BI), (20) Stroke Impact Scale, (26) Beck Depression Inventory Short Form, (27) Self Reporting Questionnaire, (28) and DSM-V criteria for major depression (29). For ischemic strokes, etiologies are defined according to TOAST criteria (30).

In order to characterize brain lesions, magnetic resonance imaging (MRI) is performed in all patients before the first session of treatment, except in the case of contraindications, on a 3 T Phillips scanner, and include high-resolution 3D T1-weighted structural images (resolution = 1 mm^3^, matrix size = 240 × 240 mm^2^, field of view = 240 × 240 mm^2^, TR = 7 ms, TE = 3.2 ms, TI = 900 ms, flip angle = 8 degrees) and axial fluid-attenuated inversion recovery (FLAIR) and T2 images (4.5 inclx 4.5 × 4.5 mm^3^). In addition, diffusion sensitized gradients (voxel size = 2 mm, isotropic; TR = 10200 ms; TE = 103 ms) are applied along 64 collinear directions with a b value = 1000 s/mm^2^. In addition, two diffusion-weighted B0 images are obtained.

Lesion locations are defined by an experienced radiologist by evaluation of FLAIR, T2 and T1-weighted images as: right/left; frontal/temporal/occipital/parietal/insular; corticosubcortical, cortical or subcortical; with or without involvement of the precentral gyrus, postcentral gyrus, centrum semiovale, corpus callosum, posterior limb of the internal capsule, thalamus, basal ganglia, mesencephalon, pons or medulla.

In order to characterize the severity of motor involvement from a neurophysiological perspective, the presence or absence of motor evoked potentials to transcranial magnetic stimulation (TMS) is also registered at baseline, in the absence of contraindications (31). A safety screening questionnaire is filled before the procedure, as previously described (32). TMS is delivered to the affected hemisphere at paretic abductor pollicis brevis “hot spot” through a figure-of-eight shaped coil (Double 70 mm coil, maximum dB/dT, 25 kT/s) held by an investigator, connected to a Magstim 2002 monophasic stimulator (MagStim, UK). EMG activity was recorded at rest from surface electrodes placed over the affected APB. EMG responses are amplified (x1000), filtered (2 Hz−2 kHz) and sampled at 5 kHz with a computerized data acquisition system built with the LabVIEW graphical programming language (33). The intervals between TMS pulses are randomized between 5 and 7 s. If no motor evoked potentials can be elicited at 100% of the stimulator's output, TMS is then delivered through a MCF-65 figure-of-eight shaped coil [outer diameter, 75 mm; maximum initial dB/dT, (33) kT/s near the coil surface] connected to a MagPro X Compact (MagVenture). If no MEPs are registered at 100% of the stimulator's output, they are registered as “absent.”

### Randomization, Allocation Concealment and Blinding

Subjects are randomized by the Principal Investigator (PI) with a basic random number computerized generator (randomization.com) in blocks of four, to active or sham RPSS in a 1:1 ratio. The randomization schedule is concealed in a locked cabinet accessed only by the PI and the investigators who administer RPSS.

Participants and investigators who assess outcomes are blinded to the interventions performed. Subjects are blinded to the experimental hypothesis and are not allowed to discuss their experience during the interventions with the researchers involved in assessment of outcomes or with other subjects. The clinical research forms of the blinded intervention are kept concealed in a locked cabinet. After each intervention session, subjects are asked: do you think your nerves were stimulated (yes/no)? Do you think your hand is different (worse/better/no change)?

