### Sample Size

We planned to include up to 40 patients and to determine the final sample size after evaluating the results of the first twenty patients included in the trial in regard to the MCID of the primary outcome (change in WMFT, Functional Ability Scale at 6 weeks compared to baseline).

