### Data Analysis

Analysis of variance with repeated measures or generalized estimating equations models with factors GROUP (active or sham) and TIME (baseline, 3, 6 weeks) will be performed, according to the distribution of the data. After all follow-ups have been completed, analyses will be performed with factors GROUP (active or sham) and TIME (baseline, 3, 6, 10, and 18 weeks). If there is an imbalance in Fugl-Meyer scores between the groups, then the analysis will be adjusted for baseline severity.

Also, the percentages of patients in the active and sham groups who will attain gains equal or larger than MCID in the WMFT and MAL, FMA-UL at 6, 10, and 18 weeks will be compared with chi-square tests or Fisher's exact tests.

Compliance with the interventions will be compared in the active and sham groups with Mann–Whitney tests.

Intention-to-treat (ITT) and per-protocol analyses will be performed. For intention-to-treat analysis, missing observations will be imputed with the Last Observation Carried Forward (LOCF).

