The proposed protocol will thus provide novel information about the effects of RPSS as an add-on intervention to motor training, under a protocol adapted to a developing-world environment, with shorter duration of treatment sessions, distributed over a longer period of time. Furthermore, the protocol has other differences in comparison to the paradigm applied by previous studies: (11, 46) first, recurrent strokes are included in the present protocol but were excluded by others (11, 46). Recurrent strokes are more common in developing countries such as Brazil compared to developed countries, and represented the most common reason for exclusion (45%) in a prior study of neuromodulation in stroke rehabilitation in Brazil (47). Because this protocol intended to be applied in a developing country, recurrent strokes were not excluded.

Second, while Carrico et al. (11) and Yadav et al. (46) administered RPSS to the Erb's point to provide brachial plexus stimulation, in addition to the median and radial nerves, in the current protocol RPSS is administered to the median, radial and ulnar nerves on the wrist/arm as previously reported (33). RPSS with Erb's point stimulation had not been described when the current protocol was designed, while nerve stimulation on the wrist/arm had been previously shown to be well-tolerated (10).

Follow-ups will continue up to 3 months post-treatment in the current protocol, providing information about long-term duration of effects of RPSS as an add-on intervention to treatment. Also, the evaluation of outcomes at 3 weeks aims to investigate whether 9 sessions of treatment lead to similar effects, compared to 18 sessions of treatment. If this hypothesis is proven correct, larger multicenter studies could be conducted faster, and at lower costs. According to current standards of payment of rehabilitation therapy and interventions of non-invasive peripheral stimulation in public health services in Brazil (http://sigtap.datasus.gov.br/tabela-unificada/app/sec/inicio.jsp), the costs of the entire treatment would be approximately 700 Brazilian reals (or 155 dollars).

Finally, detailed imaging data, including DTI analysis, is used in the proposed protocol in order to characterize the degree of involvement of the corticospinal tract, key to motor recovery after stroke, (48) in both the active and sham groups.

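### Allocation in plain blocks of four leaves upper-limb severity to chance in a trial of at most 40 patients, and severity enters the analysis only if an imbalance is seen

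*Protocol article*

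**What the plan says.** - **Allocation.** Under Randomization, Allocation Concealment and Blinding, patients are allocated "in blocks of four, to active or sham RPSS in a 1:1 ratio". No stratum and no minimisation factor is named.
- **Severity range.** Table 1 admits "a score between 7 and 50 in the Fugl-Meyer Assessment", on a scale of 0 to 66. The score decides eligibility, so it is known before allocation.
- **Size.** The Sample Size section says "We planned to include up to 40 patients", and that the investigators will "determine the final sample size after evaluating the results of the first twenty patients included in the trial".
- **Analysis.** The Data Analysis section fits repeated-measures ANOVA or GEE with group and time. Baseline severity is added conditionally: "If there is an imbalance in Fugl-Meyer scores between the groups". The sentence sets no threshold. Responder percentages are compared by chi-square or Fisher's exact tests, which take no covariate.

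**The concern.** Fugl-Meyer is the only variable whose imbalance the plan says would change the analysis, so the authors evidently regard it as prognostic. Yet the allocation does nothing to balance it, although the score is at hand when each patient is allocated and the group is small and heterogeneous.

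If the arms do differ in severity, three results become harder to read: the look at the first 20 patients, for which the article describes no adjustment; the default model without a severity term; and the responder comparisons, which the conditional adjustment cannot reach. In a trial this small, a visible severity gap can by itself make a reader discount the result, whichever way it falls.

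**Working it through.** The article states no probability of imbalance and gives no calculation behind the figure of 40, so there is no figure of the plan's to reproduce. The check asks how large a chance difference in mean Fugl-Meyer score this allocation permits.

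**Inputs from the article.** Blocks of four, 1:1; 20 patients (10 per arm) at the look; at most 40 (20 per arm); scores 7 to 50.

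**Assumption.** The Fugl-Meyer SD is not given. The upper end is a uniform spread over the 44 integer scores: SD = √((44² − 1)/12) = √161.25 = 12.7. The lower end is a concentrated case mix with SD about 8.

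**Unstratified allocation.** SE of the difference in arm means = SD × √(2/n per arm). P(|difference| ≥ 5) = 2 × (1 − Φ(5/SE)).

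| SD | n per arm | SE | P(≥ 5 points) |
|---|---|---|---|
| 8 | 10 | 3.58 | 16% |
| 8 | 20 | 2.53 | 5% |
| 10 | 10 | 4.47 | 26% |
| 10 | 20 | 3.16 | 11% |
| 12.7 | 10 | 5.68 | 38% |
| 12.7 | 20 | 4.02 | 21% |

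Simulation of the blocks agrees: 15-38% at 20 patients and 4-22% at 40. In the narrow case, truncation to 7-50 brings the realised SD to about 7.7, which explains the slightly lower figures. Without assuming an SD: a half-SD difference is 0.5/√(2/20) = 1.58 SE at 40 patients (about 11%, 1 in 9) and 0.5/√(2/10) = 1.12 SE at 20 (about 26%, 1 in 4).

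**Validity.** With uniform scores, 40 patients and an assumed correlation of 0.3-0.7 between Fugl-Meyer and outcome, the simulated type I error without adjustment is about 5% overall. Among the trials that happen to have a gap of 5 or more points it is about 8-15% unadjusted and 4-6% with Fugl-Meyer as covariate.

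**Two strata (7-28 and 29-50), simulated; P(≥ 5 points) at 40 patients.**

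| Case mix | No strata | Strata from patient 21 | Strata from patient 1 |
|---|---|---|---|
| Uniform | 21-22% | 12-13% | 2% |
| Normal, SD 9, truncated | 6-7% | 3% | 0.2% |

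Starting at patient 21 is itself an assumption: the Discussion shows that enrolment had begun, but the article does not say how many patients are already allocated. With that start, the probability at the 20-patient look does not change.

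**Gain from a fixed covariate at 40 patients.** Let r be the correlation of Fugl-Meyer with the analysed outcome, here change in WMFT. The variance ratio, adjusted to unadjusted, is about (1 − r²) × (N − 3)/(N − 4) = (1 − r²) × 37/36.
- r = 0.1: 0.99 × 1.028 = 1.018, a loss of about 2%.
- r = 0.3: 0.91 × 1.028 = 0.935, a gain of about 6-7%.
- r = 0.5: 0.75 × 1.028 = 0.771, a gain of about 23% (22% by simulation).

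**Cost in arm sizes.** With two strata, incomplete blocks left the simulated arms unequal by at most 4 patients, on average about 0.8.

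**The case against.** The case on the other side is substantial, and several parts of it stand.

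- **The plan does not predict imbalance.** A reader might infer that the authors expect the arms to differ. The sentence is conditional: it foresees the possibility and no more.
- **There is no bias on average.** A reader might also take the missing strata for confounding. Chance imbalance is already part of the standard error, and overall type I error stays near 5%.
- **Baseline is partly in the analysis.** The Sample Size section defines the primary outcome as change from baseline, time includes baseline, and responders are counted by gains. A stable difference in level is therefore largely removed. What matters is the correlation of Fugl-Meyer with change in WMFT, which the article does not give.
- **The upper figures use the widest case mix.** Excluding patients without voluntary wrist extension may thin the lowest scores. At SD 8 the risk with 40 patients is only 4-5%.
- **The full benefit of strata needs them from the first patient.** A figure of 2% or below cannot be claimed for a change made during enrolment.
- **A remedy is already planned.** It is conditional, has no stated threshold and does not reach the responder tests, so it answers the point only in part.

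A reader might go further and ask for motor evoked potential status in the model, because "the presence or absence of motor evoked potentials to transcranial magnetic stimulation (TMS) is also registered at baseline" and the Discussion speaks of "the degree of involvement of the corticospinal tract, key to motor recovery after stroke". The latter sentence concerns diffusion imaging, and the evoked potentials are recorded to describe patients, only where there is no contraindication. The article does not support adding that factor.

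**Conclusion.** The point holds as a design weakness, not as an error or contradiction. Nothing in the allocation balances the one variable that the plan singles out, and the analysis takes it up only after looking at the data.

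The risk of a 5-point gap is modest to appreciable, and its size rests on the assumed Fugl-Meyer SD; only the half-SD figures are free of that assumption. The effect on the primary comparison cannot be sized from the article, because it depends on an unknown correlation with change: from no gain at all near r = 0.1 to roughly a fifth of the variance at r = 0.5. The case for acting is that the remedy is cheap and uses a score already collected.

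**What to change.** 1. **Patients still to be randomised.** Generate two permuted-block lists by screening Fugl-Meyer score, for example 7-28 and 29-50, with the same tool and the same 1:1 ratio.
2. **All patients, including those already allocated.** Include Fugl-Meyer score (or the stratum) as a fixed term in the group comparison whatever the observed balance, in place of the conditional rule, and apply the same term at the 20-patient look. Take the score obtained at screening: the other baseline outcomes are measured on the day of the familiarisation session, when the allocated stimulation is already given.
3. **Responder comparisons.** Use a Mantel-Haenszel or exact test stratified by the same split.
4. **Reporting.** State how many patients had been randomised when the strata began, since the benefit of step 1 depends on it. Steps 2 and 3 do not.

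The cost is a short amendment and two lists instead of one, with no extra patients or procedures. Arm sizes may differ by up to 4 (on average under 1), one degree of freedom is lost, and precision could fall very slightly if Fugl-Meyer turns out to be almost unrelated to change in WMFT.

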### Data and Safety Monitoring Plan

The P.I. and the research coordinator are responsible for ensuring absolute compliance with eligibility criteria and data confidentiality. All research materials will be kept locked in cabinets. Only the research team members will have a password to use the computer where the data will be acquired and stored. Adverse events are monitored by using Common Toxicity Criteria Manual of the National Cancer Institute as guidance, and reported to the Ethics Committee and to the NIH. Progress reports are sent to the Ethics Committee every 6 months. Serious adverse event reports must be reported to the Ethics Committee within 24 h.

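### The PI makes and can open the allocation list and also shares responsibility for eligibility, so the stated arrangement does not rule out foreknowledge of the next assignment at entry

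*Protocol article*

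**What the plan says.** Three places in the protocol article bear on this.

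- *Randomization, Allocation Concealment and Blinding* names the person who allocates: "Subjects are randomized by the Principal Investigator (PI) with a basic random number computerized generator (randomization.com) in blocks of four", with a 1:1 ratio. On custody it says: "The randomization schedule is concealed in a locked cabinet accessed only by the PI and the investigators who administer RPSS".
- *Data and Safety Monitoring Plan* gives the duty over entry: "The P.I. and the research coordinator are responsible for ensuring absolute compliance with eligibility criteria and data confidentiality".
- *Familiarization* has RPSS given according to the randomized arm at the familiarization session, with all baseline outcomes evaluated on the same day. The order within that day is not stated.

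The blinding statements, under *Design* and again under *Randomization, Allocation Concealment and Blinding*, cover participants and outcome assessors. The PI is not listed as blinded. The RPSS section keeps the RPSS staff out of FES, training and outcome evaluation.

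**The concern.** Allocation concealment and blinding are different safeguards. Concealment means that whoever influences entry cannot know the next assignment until the patient is irrevocably in. Blinding acts after that. The locked cabinet serves blinding, because it keeps the schedule from participants and assessors. It does not give concealment with respect to the PI, who can open it and who shares the duty over eligibility.

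This matters because at least one entry criterion in Table 1 calls for judgement: "Ability to comply with the schedule of interventions and evaluations in the protocol". The Fugl-Meyer window of 7 to 50 also admits patients of widely differing severity. If the next arm is known, a borderline patient can be admitted, declined or deferred accordingly, without anyone intending harm. In a single-centre trial of at most 40 patients, a modest prognostic difference created in this way could be read as a treatment effect. Blinded outcome assessment does not remove a difference already present at entry.

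**Working it through.** The plan states no figure on this point, so there is none to reproduce. The check sets the passages side by side and then asks how predictable the sequence is.

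**1. Who can see what, and who answers for entry**

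| Role | Access to the schedule | Documented role in entry |
|---|---|---|
| PI | yes; also performs the randomization | yes, shared responsibility for eligibility compliance |
| Research coordinator | not listed | yes, shared responsibility |
| RPSS investigators | yes | none stated |
| Outcome assessors | no, blinded | none stated |

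Only the PI has both list access and a documented responsibility for entry. The article mentions no third-party holder, no one-at-a-time release, and no rule that eligibility is closed before an assignment can be seen.

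**2. Foreknowledge with the list**

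Inputs: up to 40 patients (*Sample Size*), blocks of four, 1:1. This gives 40 / 4 = 10 blocks and 20 per arm. If the whole list is readable, up to 40 of 40 assignments can be known in advance, whatever the block size. If an independent holder releases each arm only after irrevocable entry, advance knowledge from the list falls to 0 of 40.

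**3. Predictability without the list**

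This applies to someone who knows all past assignments and the block size (2 active, 2 sham per block) and always guesses the under-represented arm.

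- 1st place: 1/2 correct.
- 2nd place: 2/3 correct.
- 3rd place: the first two are equal with probability 1/3, and then the 3rd is certain; otherwise it is a coin toss. 1/3 + (2/3)(1/2) = 2/3.
- 4th place: always certain.

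Correct guesses: (1/2 + 2/3 + 2/3 + 1)/4 = 17/24 = 70.8%, or 28.3 of 40, against 20 by chance. Certain assignments: (1/3 + 1)/4 = 1/3, or 13.3 of 40. A random mix of blocks of 4 and 6, simulated 20,000 times, still allows about 27.6 of 40 correct guesses (69%). Custody of the list is therefore what matters, and block size is minor.

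**4. What a steered difference could do (illustration only)**

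Assumptions, none of them from the documents: 20 per arm analysed, two-sided alpha 0.05, no true effect, normal approximation, and a prognostic difference of d SD between arms created at entry. The standard error in SD units is √(2/20) = 0.316. The chance of a significant result favouring the better-prognosis arm is Φ(d/0.316 − 1.96).

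| d (SD) | Chance of a false result in that direction |
|---|---|
| 0 | 2.5% |
| 0.2 | 9% |
| 0.3 | 16% |
| 0.5 | 35% |

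The documents give no basis for choosing a value of d.

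**5. Does the planned analysis repair it?**

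Only in part. *Data Analysis* adjusts for baseline severity if Fugl-Meyer scores turn out imbalanced. Selection on something else, such as expected adherence, would not be covered.

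**The case against.** The strongest reply is that the text does not say that the PI decides who enters. The eligibility duty is shared with the coordinator, it stands in a monitoring section and can be read as oversight, and no section says who screens, consents or enrols. The article also gives access to the cabinet but not the release procedure, so sealed sequential assignments inside it cannot be excluded. Both points stand. They rule out saying that the PI determines eligibility, or that all 40 assignments are in fact seen in advance. They do not remove the defect. The article states who allocates, who may open the schedule and who answers for eligibility, and together these leave foreknowledge open to one person. That is a stated arrangement, not a detail left to a fuller document.

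A reader might also draw three stronger conclusions that the documents do not support:

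- *That the RPSS operators can steer enrolment.* They can open the schedule, but no section gives them a part in recruitment or eligibility.
- *That blocks of four are themselves a main flaw.* The 1/3 and 70.8% figures apply to someone who knows only past assignments, and the documents identify no such person. Those documented as having access to the assignments already have the list.
- *That enrolment was steered.* Nothing in the article suggests it.

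Extensive baseline data and the conditional Fugl-Meyer adjustment are real but partial mitigation. Finally, enrolment had already begun when the article was written and the number of patients remaining is not given, so the benefit of a change now cannot be quantified.

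**Conclusion.** The concern holds as a design defect in custody of the list. The PI produces and can open the allocation schedule and also shares responsibility for eligibility, so the arrangement as written does not prevent a person with responsibility for entry from foreseeing the next assignment. The locked cabinet protects only the blinding of participants and assessors.

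The extent of possible foreknowledge ranges from none, if an undescribed release procedure prevents it, to 40 of 40. The resulting bias has no size in the documents; the 9% to 35% false-positive range rests wholly on assumed differences of 0.2 to 0.5 SD. The conclusion needs no assumption that anyone acted on the list. It rests only on the stated access and the stated duty.

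One neighbouring matter is separate and secondary. Subjects are "not allowed to discuss their experience during the interventions with the researchers involved in assessment of outcomes or with other subjects", and this rule does not name the FES and training therapists. That bears on how patients are treated after entry, not on concealment.

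**What to change.** For the patients still to be enrolled:

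1. Have a new list generated and held by someone in the institution with no role in recruitment or eligibility, or by a web system.
2. Remove the PI's access to it. RPSS operators receive only the assignment of the patient in front of them, not the list.
3. Release one assignment at a time to the RPSS operator, only after consent and eligibility sign-off are recorded.
4. Fix the order of the familiarization day so that all baseline outcomes are recorded before the assignment is released and RPSS is given.
5. Record the date of the change and how many patients were allocated under each arrangement. If the old list is cut within a block, the resulting imbalance is at most two patients.

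The cost is one amendment, a small administrative task for the list holder and a set sequence on the familiarization day. The change cannot repair entries already made.

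Varying the block size is optional and gains little (70.8% to about 69% guessable). Extending the no-discussion rule to the FES and training therapists can go into the same amendment as a separate item.
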